## 5.0 STUDY PROCEDURES

### 5.1 Study visits and measured parameters

Standard admission group:

An activity tracker (Vitalpatch-discussed under section 5.3) will be placed on all subjects in the control group during admission only. Subjects in the control group will receive usual care at the hospital, from an attending general internist.

Rural home hospitalization group (intervention group):

Each day, the RHH clinical team will make in-person and/or virtual visits to the patient's home. These are personnel who have been trained in home health and carry out home health as per the usual care they deliver. They have received additional training in RHH. The RHH module offers most of the same medical components that are standard of care in an acute care hospital (**Table below**). The typical staff (MD, RN, or paramedic), diagnostics (blood tests, vital signs, telemetry), intravenous therapy, and oxygen/nebulizer therapies will all be available.

RHH improves upon the components of a typical ward's standard of care in several ways:

- Minimally invasive continuous vital signs, telemetry, and activity tracking
- 24/7 clinician video visits;
- Ambulatory/portable infusion pumps that can be worn on the hip;

| Component     | Module                                                                                                                                                                                                                                                                                                                                                                                                                                                                                                                 |
|---------------|------------------------------------------------------------------------------------------------------------------------------------------------------------------------------------------------------------------------------------------------------------------------------------------------------------------------------------------------------------------------------------------------------------------------------------------------------------------------------------------------------------------------|
| Personnel     | [figure not shown] [figure not shown]
Nurse/Paramedic 
 
• 2 daily visits (1 in-person; 1 virtual)
 
• Medication administration
 
• IV access management
 
• Education
 

Physician 
 
• 1 daily interaction
 
• Medical decision making
 
 |
| Diagnostics   | Point of care: BMP, Hgb/Hct, PT/INR, ultrasound, x-ray, PFTs, ECG                                                                                                                                                                                                                                                                                                                                                                                                                                                      |
| Pharmacy      | Any inpatient medication, most any route                                                                                                                                                                                                                                                                                                                                                                                                                                                                               |
| Equipment     | Ambulatory infusion pump, peripheral IV, oxygen concentrator                                                                                                                                                                                                                                                                                                                                                                                                                                                           |
| Communication | Telepresence/virtual visits                                                                                                                                                                                                                                                                                                                                                                                                                                                                                            |
| Monitoring    | Wireless remote vital signs, telemetry, activity tracking                                                                                                                                                                                                                                                                                                                                                                                                                                                              |

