#### Clinician inclusion criteria:

- The rural home hospital clinical team will be identified by the site PI at each study site prior to the start of the study. The site PI will recruit local RNs and/or EMT-Ps, and attending physicians (MD) to deploy and provide rural home hospital care.
- Any member of the rural home hospital clinical team (a clinician providing care in the home) who will be participating in research activities, including the screening and recruitment of patients for the rural home hospital intervention and/or providing care to rural patients that enroll in the intervention.

Sites without continuous monitoring will make amendments to the above inclusion criteria

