## 5.3 Devices to be used

- Home hospital employs standard devices during the usual care of hospitalized patients. For example, a nebulizer machine.
- Telehealth platform: Biofourmis AI platform, biovitals® Hospital@Home. Biofourmis has completed their cybersecurity assessment and has been vetted by the Partners data sharing committee. The Biofourmis tablet serves as the communication hub and facilitates videoconferencing between the patient and physician/RN/EMT-P and it captures biometric data.
- Home hospital additionally employs
  - Vital signs monitoring patch: Vital Connect VitalPatch (FDA cleared application/use)
    - The patch will be placed on subjects in both groups, it includes a built-in activity tracker (we will use the activity tracker for control group subjects during hospital admission)
  - Ambulatory infusion pump: Smiths Medical CADD Solis VIP (FDA cleared application/use)
  - Point of care diagnostic meter: Abbott iSTAT (FDA cleared application/use) or Siemens EPOC (FDA cleared application/use)
  - Digital stethoscope (Eko; FDA cleared application/use)
  - Point of care ultrasound (Philips Lumify; FDA cleared application/use)

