|                                        |                                                              |           |
|----------------------------------------|--------------------------------------------------------------|-----------|
| MRSA                                   | As above.                                                    | Daily     |
| New arrhythmia                         | As above.                                                    | Daily     |
| Hypokalemia                            | As above.                                                    | Daily     |
| Acute kidney injury                    | As above.                                                    | Daily     |
| Medication error                       | As above.                                                    | Daily     |
| Unanticipated mortality                | As above.                                                    | Daily     |
| Loss of consciousness                  | As above.                                                    | Daily     |
| Transfer back to hospital a | RA via MD/RN                                                 | Discharge |
| Unplanned mortality during admission   | RA via MD/RN for home patients; MD EHR review for inpatients | Discharge |
| Unplanned 30-day mortality             | RA via pt/caregiver call                                     | +30       |

a: intervention arm only

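### New arrhythmia is recorded in both arms without a common definition, although rhythm monitoring differs by arm at sites with continuous monitoring, so the chance of recording the same event can depend on allocation

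*Protocol*

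**What the plan says.** **Home arm.** Section 5.1 states that "RHH improves upon the components of a typical ward's standard of care in several ways", and the first item listed is "Minimally invasive continuous vital signs, telemetry, and activity tracking". The monitoring row of Table 1 in the same section reads "Wireless remote vital signs, telemetry, activity tracking". Section 8.0 repeats continuous telemetry as a clinical improvement on the standard of care.

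**Control arm.** Section 5.1: "An activity tracker (Vitalpatch-discussed under section 5.3) will be placed on all subjects in the control group during admission only". Section 5.3 confirms that both groups wear the patch and adds that "we will use the activity tracker for control group subjects during hospital admission". The word 'only' in 5.1 limits the time of wear, not the function. Still, neither section provides for anyone to read rhythm data from control patches. Controls otherwise receive usual hospital care.

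**Outcome.** The Safety table in 5.5.3 lists "New arrhythmia", obtained daily. Its source carries down from the rows above: report by the physician or nurse for home patients, and physician review of the health record for inpatients. Only transfer back to hospital is marked as intervention-only. The table gives no definition of the event.

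**Sites.** Section 3.1 notes that "Sites without continuous monitoring will make amendments to the above inclusion criteria". Section 3.2 has the parallel sentence for exclusions, and section 6.1 plans a subgroup analysis of continuous against intermittent monitoring sites. The number of sites of each type is not stated.

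**The concern.** A recorded arrhythmia needs both the rhythm change and someone or something to notice it. Where the home arm has continuous telemetry and controls have it only if the ward supplies it, the second condition differs by arm. Equal true incidence can then give unequal counts.

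The trial enrols patients with heart failure and with atrial fibrillation (section 3.1), so rhythm events are a relevant safety measure. Section 8.0 anticipates fewer complications at home, so the safety figures are likely to be read by arm. An excess at home could reflect closer watching, and a real excess could be dismissed as closer watching. The row as written does not let a reader separate the two.

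The different reporting routes are a second source of unequal capture, of unknown direction. Making those routes identical would not cure the first problem, because a chart cannot show a rhythm change that nobody was monitoring for.

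**Working it through.** The protocol gives no arrhythmia rate, no detection rate and no share of controls on telemetry, so it has no figure to reproduce. The calculation below is an illustration.

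**Inputs from the protocol:** three sites (section 3.3), and 66 patients per arm with 44 in total per site, i.e. equal site sizes (section 6.1, power analysis).

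**Assumptions, not in the protocol:**
- True incidence is the same in both arms and at all sites.
- Detection is 0.9 under telemetry.
- Detection without telemetry is d = 0.4 (range 0.3 to 0.6).
- The share of controls on ward telemetry is t = 0.5 (range 0.25 to 0.75), the same at every site.
- Home patients at an intermittent-monitoring site have detection d.

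**Formulas**, with k the number of intermittent sites out of three:
- Control detection: C = 0.9t + d(1 − t) = 0.45 + 0.20 = 0.65
- Home detection: H = [(3 − k) × 0.9 + k × d] / 3
- Apparent risk ratio with no true difference: H / C

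| Intermittent sites | H | H / C | Range over d and t |
|---|---|---|---|
| 0 | 0.900 | 1.38 | 1.09 to 2.00 |
| 1 | (1.8 + 0.4)/3 = 0.733 | 1.13 | 0.93 to 1.56 |
| 2 | (0.9 + 0.8)/3 = 0.567 | 0.87 | 0.67 to 1.11 |

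The ends of the ranges come from these corners:
- k = 0: 0.9/0.825 (d = 0.6, t = 0.75) and 0.9/0.45 (d = 0.3, t = 0.25).
- k = 1: 0.7/0.75 (d = 0.3, t = 0.75) and 0.7/0.45 (d = 0.3, t = 0.25).
- k = 2: 0.5/0.75 and 0.5/0.45 (the same two corners).

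**Within one site**, at the midpoint values, the ratio is 0.9/0.65 = 1.38 where monitoring is continuous and 0.4/0.65 = 0.62 where it is intermittent. At an intermittent site the imbalance vanishes only if no controls have telemetry (t = 0, so C = d); otherwise it reverses. The pooled ratio crosses 1 between one and two intermittent sites.

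**As counts**, at an assumed true rate of 10% and 66 per arm, the expected recorded events (home against control) are 5.9 against 4.3, 4.8 against 4.3 and 3.7 against 4.3 for k = 0, 1 and 2 (66 × 0.10 × detection). With equal detection the ratio is 1.00.

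**The case against.** **Telemetry is also hospital care.** Section 5.1 names it among typical hospital diagnostics, and the early-transfer example in section 3.3 describes an inpatient with heart failure who needs telemetry. This stands. A reader might infer that telemetry-only episodes would be absent from most control charts; the protocol does not support that. But if nearly all controls were on telemetry, the gap would close only by contradicting the improvement claimed in 5.1 and 8.0.

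**The direction is not settled.** A reader might infer that the home arm will show an excess, or apply 1.09 to 2.00 to the whole trial. That range requires continuous monitoring at every site, which sections 3.1, 3.2 and 6.1 do not assume.

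**Little formally rests on this row.** It is exploratory. Section 6.1 names models only for the primary and secondary outcomes, and arrhythmia is not among the events that section 9.0 sends to the monitoring committee. A reader might infer that the trial must establish safety on this measure, but the aims in section 2.0 are cost, days at home, physical activity and readmission. All of this stands.

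**Events are clinician-reported, not raw patch output.** Correct, and the only alarm described in 5.1 concerns delayed data transfer, so 90% home detection is an assumption. Telemetry nevertheless informs the clinicians who report.

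**Other documents may define the event.** The analysis plan, case report form or Monitoring Plan may do so. That could settle the definition, but it could not recover rhythm events never looked for in controls.

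**The planned monitoring subgroup.** It separates types of site but does not equalise the arms within a site.

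**Conclusion.** The point holds in a limited form. At sites with continuous monitoring, the protocol gives the arms different rhythm surveillance and counts arrhythmia in both without a definition that is neutral to it. Detection can therefore depend on allocation.

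Neither the size nor the overall direction can be fixed from the protocol. The illustrative ratios run from 1.38 down to 0.87 as the number of intermittent sites goes from none to two, and they rest on assumed detection rates and an assumed telemetry share. At a 10% true rate the expected difference is under two events per 66 patients. The consequence is a safety row that cannot be interpreted by arm, not a threat to the trial's main conclusion; the primary cost result is not directly affected. The change is worth making because it is small.

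**What to change.** In the Safety table of 5.5.3, define the row for both arms as: new arrhythmia documented on a 12-lead ECG, or charted by the treating physician as a new diagnosis leading to treatment, consultation or transfer, from randomisation to discharge. In addition:

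- Report arrhythmias seen only on the patch separately and descriptively for the home arm, outside the between-arm comparison.
- Present the measure by continuous and intermittent monitoring site, in line with the subgroup already planned in 6.1.
- State the monitoring difference beside any between-arm figure.

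The cost is a change to one table row and its data-collection form, plus a line in the reporting plan, with no new procedures and no change to care. Fewer events will be counted. Some imbalance will remain, because telemetry can prompt the ECG or treatment that then qualifies.

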**Table 1**

As denoted in the table above, the physician will make at least one daily virtual visit to the patient's home, facilitated by the nurse/paramedic. At the discretion of the physician and nurse/paramedic, the physician can make additional virtual visits should the patient's clinical condition require it. Similarly, the nurse/paramedic will make at least two daily visits to the patient's home. At the discretion of the physician and nurse/paramedic, the nurse/paramedic can make additional visits should the patient's clinical condition require it. This will be an ongoing twice daily discussion among clinicians, patient, and caregivers, as applicable. A patient or

549 clinician can initiate a video visit at any time. As denoted in the table above, the RHH team uses  
550 a suite of communication software to communicate with the patient and among team members.  
551 The nurse or paramedic will provide technology training to the patient (as needed) at admission  
552 and the rural home hospital team will be available to provide any technical assistance to subjects  
553 as needed.

554  
555 For patients with chronic/stable dementia, they will receive mental status assessments (eg,  
556 Confusion Assessment Method) by the home hospital RN/paramedic at each visit (at least 2  
557 daily). As is standard of care, we will take measures to avoid delirium: open blinds to allow light  
558 in during the day, minimize environmental noise, encourage typical routines to optimize eating  
559 and sleeping, and reassess medication list for culprit medications.

560  
561 Clinical parameters measured will be at the discretion of the physician and nurse/paramedic, who  
562 treat the participant following evidence-based practice guidelines, just as in the usual care  
563 setting. Monitoring will be performed by RHH clinicians. The clinical home hospital team  
564 manually checks vital signs at least daily. If deemed necessary based on a patient's acuity, the  
565 home hospital team can visit additional times. At all times, the patient and care team have 24/7  
566 access to the RHH attending physician.

567  
568 On top of this "on-the-ground" team, the home hospital attending is notified with an alarm  
569 should there be delayed data transfer. Such an alarm would cause the attending to contact the  
570 patient as deemed clinically appropriate.

571  
572 Please see below for all collected data points.

573  
574 Documentation by RN/paramedic and MD will occur via digital intake notes, daily progress  
575 notes, and discharge notes that will be compiled (on a secure shared drive) and uploaded as a  
576 scanned document to the patient's chart upon discharge.

[figure not shown]

**Figure 1** RHH flow. Note a patient may **enter** this flow from their home, a clinic, the emergency department, or the hospital floor. The patient is triaged by the RHH nurse with as needed assistance of the RHH MD. The RHH nurse/paramedic deploys in the patient's home, facilitates a medical evaluation by a remote MD, welcomes and educates the patient, and sets up monitoring and communication technology. The nurse rounds at least once daily in person, facilitating an interaction with the RHH MD. Finally, the patient is discharged using the same criteria for discharge as would be used in a traditional hospital (ability to perform activities of daily living given supports in the home).

## 5.2 Drugs to be used

Only medications used in the usual care of hospitalized patients will be used. For example, a patient with pneumonia might receive guideline-based antibiotics with ceftriaxone and azithromycin.

## 5.3 Devices to be used

- Home hospital employs standard devices during the usual care of hospitalized patients. For example, a nebulizer machine.
- Telehealth platform: Biofourmis AI platform, biovitals® Hospital@Home. Biofourmis has completed their cybersecurity assessment and has been vetted by the Partners data sharing committee. The Biofourmis tablet serves as the communication hub and facilitates videoconferencing between the patient and physician/RN/EMT-P and it captures biometric data.
- Home hospital additionally employs
  - Vital signs monitoring patch: Vital Connect VitalPatch (FDA cleared application/use)
    - The patch will be placed on subjects in both groups, it includes a built-in activity tracker (we will use the activity tracker for control group subjects during hospital admission)
  - Ambulatory infusion pump: Smiths Medical CADD Solis VIP (FDA cleared application/use)
  - Point of care diagnostic meter: Abbott iSTAT (FDA cleared application/use) or Siemens EPOC (FDA cleared application/use)
  - Digital stethoscope (Eko; FDA cleared application/use)
  - Point of care ultrasound (Philips Lumify; FDA cleared application/use)

#### **5.4 Procedures/surgical interventions**

Home hospital employs the same standard procedures used during the usual care of hospitalized patients. For example, peripheral venipuncture. Need for surgery is a relative exclusion criterion.

#### **5.5 Data to be collected and when the data will be collected**

For both groups we will administer a survey to patients on admission, at discharge, and 30-days post-discharge. For both groups, we will administer a survey to caregivers at admission and 30-days post-discharge.

For the intervention arm only, within 30-days of discharge we will conduct qualitative interviews with the patient and their caregiver (if their caregiver consented to participate in the study, caregiver participation is not required for patient enrollment in this study) (please see more details below).

For the intervention arm, we will ask the rural home hospital MD to complete the MD AM Report each morning and the RHH RN/EMT-P to complete the Nursing visit form after each patient visit. Twice a week we will send the RHH clinicians the Clinician process measures survey. Post-discharge we will conduct qualitative interviews with rural home hospital clinicians only (please see more details below).

For both groups:

Clinical and administrative data will be extracted from electronic sources (e.g., enterprise data warehouse, electronic health record (EHR) at study sites). Cost data for the hospitalization and post-discharge period will be obtained from study site financial personnel using direct cost accounting methods. We will also collect information from patients and caregivers using IRB approved surveys and standardized questionnaires (see below). All data will be collected by trained study staff and inputted on a Partners encrypted shared drive. Data collected from filed research collection (including patient surveys) will be stored in REDCap (Research Electronic Data Capture, Vanderbilt University, Nashville, TN), which is fully HIPAA-compliant secure web application.

- All data collected at Alberta Health Services (Wetaskiwin Hospital) will also be stored on MGB REDCap

We will utilize the REDCap+Twilio module for texting. We will use this system to send out text reminders to study subjects to complete REDCap surveys. All the participant data is stored in REDCap (names, emails, phone numbers). Twilio is used to send the text + survey link. When the respondent touches the link, their browser opens on their smart phone and they complete the survey in the secure website. No PHI or PII will be included in the text of the text message. Message text is defined by the study team and approved by the IRB and study subjects will provide written or electronic consent (through REDCap) to receive communication via text message.

Patient and caregiver surveys may be administered in-person, by email, by phone, text message (if patient/caregiver has consented to receiving text messages) (REDCap +Twilio module for texting) or by paper mail. Clinician surveys will be emailed or sent by text message to clinician subjects through REDCap.

We have attached the following surveys (paper version) to this protocol submission:

- Caregiver admission survey\_PAPERSURVEY\_Feb2022
- Caregiver post-discharge survey\_PAPERSURVEY\_Feb2022
- Patient discharge survey\_PAPERSURVEY\_Feb2022
- Patient post-discharge survey\_PAPERSURVEY\_Feb2022

The remaining patient and clinician surveys will be electronic (REDCap):

- Patient admission survey
- All clinician forms and surveys
  - MD AM report
  - Nursing visit form
  - Clinician process measures survey

Patient surveys:

- In-person: research assistant/coordinator may administer the patient survey in-person.
- Email: the surveys will be sent by email through REDCap

- Text message: the surveys will be sent by text message through REDCap (REDCap + Twilio module)
- Phone: research assistant/coordinator will administer the paper survey over the phone and input the data into REDCap
- Paper mail: the paper survey will be sent by mail through USPS to the subject. We will also include a pre-addressed/stamped envelope for participants to mail their completed survey back to the study team.

